Until recently, the consensus guidelines on vascular access strongly preferred AVFs over AVGs, as in some populations AVFs have a longer secondary patency for dialysis and require less frequent surgical or percutaneous interventions to maintain their patency. On the other hand, a higher proportion of AVFs than AVGs are abandoned prior to their successful use, resulting in prolonged CVC-dependence. The superiority of AVFs over AVGs has been questioned, in particular for older (≥ 60 years) adults, who currently account for 60% of patients initiating chronic HD for treatment of ESKD [1]. Contemporary observational studies comprised of large cohorts of older adults have suggested that AVGs may confer similar or better patient outcomes than AVFs [10–12]. In an intention to treat analysis, AVGs had a higher secondary patency rate than AVFs in the first 18 months of access creation [13, 14]; shorter time to access cannulation; and lower rates of adjuvant procedures than AVFs, conferring faster transition to CVC-free HD [6, 15–17]. A meta-analysis of 13 studies concluded that older patients have a 50–65% higher risk of primary AVF failure and 80% higher risk of secondary AVF failure compared with younger patients [18].

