	**Other Outcomes**			
Compare vascular access-related outcomes	AV access primary failure	Rate of AV access maturation failure	Chart review	M0-End
	Time to AV access cannulation	Successful AV access cannulation	Chart review	M0-End
	AV access patency	Duration of AV access patency (primary, assisted, cumulative)	Chart review	M0-End
	CVC-related infections	Incidence rate of CVC-related infections per 100 patient-days	Chart review	M0-End
	AV access infections	Incidence rate AV access infections requiring or not requiring hospitalization, per 100 patient-days	Chart review	M0-End
	Adjuvant procedures	Endovascular or surgical procedures on AV access	Chart review	M0-End
	AV access infection rate	Local or systemic infections related to index AV access infection (e.g., cellulitis)	Chart review	M0-End
	CVC-related infection rate	Local or systemic infections related to CVC	Chart review	M0-End
	Hospitalization rate	Date and cause of hospitalization	Chart review	M0-End
	Survival	Date and cause of death	Chart review	M0-End
Evaluate relationships between preoperative physical function and index AV access outcomes	Preoperative frailty and index AV access outcomes	Grip Strength Chair stand test Pepper Assessment Tool for Disability Clinical Frailty Scale Index AV access primary failure Time to successful cannulation of index AV access Rate of adjuvant procedures on index AV access	Patient, Physician & Chart review	M0-End
M denotes month; M0, baseline; M6, month 6 etc.				

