### New AV Access surgery after index AV access surgery

If, over the course of follow-up, the index AV access is abandoned after its creation, the plan for and choice of a subsequent, new AV access will be at the discretion of the local medical team. Participants who undergo surgery for creation of a new AV access will continue to be followed until an end-of-study event. New AV access surgery will be subject to data collection similar to that of the index AV access surgery. AV access cannulation and complications during follow-up will identify whether it corresponded to the index AV access or a new AV access.

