### Analysis for primary outcome

The primary outcome is the rate of CVC-free days per 100 patient-days. The primary analysis will be performed under the intention-to-treat principle. The outcomes will be measured from the date of randomization to the date of an end-of-study event (see **Additional file 7**) or end-of-study date, whichever comes first. For each participant, the primary outcome will be the cumulative number of days that dialysis is delivered using AV access with the at-risk time as an offset. We will compare outcomes between the treatment groups using Poisson regression, modeling the number of CVC-free days as the dependent variable with a log link, the treatment assignment as the predictor, and the natural log of number of at-risk days as an offset. Covariate adjustment will include enrollment center and history of prior AV access. Analyses will take into account events of CVC re-use after CVC-free days. Deviance residuals and the overall deviance measure will be calculated to assess the overall goodness of fit of the model as part of model diagnostics. If we observe overdispersion, we will explore the negative binomial models. Sensitivity analyses will be performed in the as-treated and per-protocol populations.

As a supporting analysis, safety analysis will be conducted to examine severe access infections defined as infections requiring hospitalization or death caused by access infection. Rates of severe infections between AVG and AVF groups will be compared using Poisson regression models. If we observe overdispersion, we will explore the negative binomial models.

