### Analysis for secondary outcomes

Access-related healthcare costs analysis will be based on the intention-to-treat principle. The costs will include index access placement (AVF or AVG), procedures required to promote study AV access maturation (angioplasty or surgical revision), procedures to maintain study AV access patency for HD after successful use (angioplasty, thrombectomy, or surgical revision), surgery to place a new vascular access (AVF or AVG) if the study AV access failed or was abandoned, procedures to promote maturation and maintain patency of all subsequent accesses, procedures of CVC exchange due to catheter dysfunction or infection, and reimbursement associated with access-related hospitalizations. Similar to our previous work, we will use the reimbursement fees established by the Center of Medicare and Medicaid Services, per each corresponding year of study, for access-related hospitalizations and inpatient or outpatient services and procedures [34]. Per-patient access cost will include the cost of all access-related procedures and hospitalizations divided by the total number of years of follow-up for that patient. As in standard economic analysis, costs will be discounted at 3% annually. Log transformation will be used to better approximate normality. A general linear model will be used to test the difference on the log scale between the fistula and graft groups. The estimates will be back transformed to represent median costs on the original scale. We will also use a generalized linear model with Gamma distribution and a log link to compare the mean access-related cost between the two groups.

Other secondary outcomes include rates of AV access maturation, rates of AV access adjuvant procedures, and rates of infectious and non-infectious vascular access (CVC or AV access) complications. Poisson regression models will be used to test the difference between AVF and AVG groups. If we observe overdispersion, we will explore the negative binomial models. Deaths will be analyzed using Cox regression models.

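### AV access maturation, most naturally a once-only yes/no outcome, is grouped with recurrent events under Poisson regression, with a remedy for overdispersion only

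*Protocol article*

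**What the plan says.** In the protocol article, Analysis for secondary outcomes, the outcomes after costs are introduced together: "Other secondary outcomes include rates of AV access maturation, rates of AV access adjuvant procedures, and rates of infectious and non-infectious vascular access" complications. One model is then assigned to the whole list: "Poisson regression models will be used to test the difference between AVF and AVG groups". The only contingency, and the different treatment of death, follow: "If we observe overdispersion, we will explore the negative binomial models. Deaths will be analyzed using Cox regression models". That paragraph names no offset, unit of analysis or variance estimator for maturation.

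Table 1 words the measure the other way round, as "Rate of AV access maturation failure", and places it under Other Outcomes. The primary model in Analysis for primary outcome uses "the natural log of number of at-risk days as an offset". The opening sentence of Outcomes and measurements says that every outcome runs from randomization to the end-of-study event.

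**The concern.** Adjuvant procedures and infections can recur in one patient, so a count model with person-time is natural for them. Maturation is different: an index access either becomes usable or does not. The article's own usage supports this reading:

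- Table 1 gives two infection outcomes a denominator of 100 patient-days, but gives maturation failure none.
- Table 1 lists time to cannulation as a separate outcome.
- The Background describes the phenomenon as a proportion: "a higher proportion of AVFs than AVGs are abandoned prior to their successful use".
- Other once-only or binary outcomes get other models: Cox for death and for primary failure in the exploratory analysis, and GEE with odds ratios for goal concordance.

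Poisson regression takes the variance to equal the mean, p. A 0/1 outcome has variance p(1 − p), which is smaller. The data are therefore underdispersed relative to the model, whereas the stated contingency deals only with overdispersion. At stake are the power and the interval width for an outcome that the article counts among several access events behind CVC-free days.

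**Working it through.** The plan states no figure for maturation, so there is none to reproduce.

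**Inputs.** n = 131 per group and a two-sided 5% test, both from the sample size section. The maturation proportions are assumptions and are varied.

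**Formulas, no offset.**
- Model-based Poisson SE of the log ratio: SE_P = √(1/(n·p1) + 1/(n·p2))
- Binomial SE of the log risk ratio: SE_B = √((1 − p1)/(n·p1) + (1 − p2)/(n·p2))
- The estimate truly varies with SE_B but is judged against 1.96·SE_P. Poisson power is therefore Φ((|log RR| − 1.96·SE_P)/SE_B), and correct power is Φ(|log RR|/SE_B − 1.96).

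**Example, 60% vs 75% matured.** SE_P = √(1/78.6 + 1/98.25) = 0.151. SE_B = √(0.40/78.6 + 0.25/98.25) = 0.087. log 1.25 = 0.223. Poisson: (0.223 − 1.96 × 0.151)/0.087 ≈ −0.84, power 20%. Correct: 0.223/0.087 − 1.96 ≈ 0.59, power 72%.

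| Modelled event (assumed) | SE_P | SE_B | Ratio | Power, Poisson SE | Power, correct SE |
|---|---|---|---|---|---|
| Failure 40% vs 25% | 0.223 | 0.185 | 1.20 | 57% | 72% |
| Matured 50% vs 65% | 0.164 | 0.108 | 1.52 | 29% | 68% |
| Matured 60% vs 75% | 0.151 | 0.087 | 1.73 | 20% | 72% |

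The first and last rows describe the same patients, coded as failure or as maturation. The article uses both codings.

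With equal proportions the ratio is 1/√(1 − p): 1.41 at 50% and 1.83 at 70%. The nominal 5% test then has a true size of 0.6% and 0.03%.

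**Simulation under no difference** (1,500 trials per setting, 131 per group, event proportions 30%, 50% and 70%, assumed dropout and follow-up):

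| Offset | Model SE / true SD | Rejection at nominal 5% |
|---|---|---|
| None | 1.15, 1.35, 1.75 | 3.1%, 0.7%, 0.1% |
| Total follow-up | 1.13, 1.33, 1.55 | 2.3%, 0.8%, 0.3% |
| Time to maturation or censoring, constant hazard | 0.98, 0.98, 1.00 | 4.7%, 5.3%, 4.7% |
| Same, but some accesses never mature and the rest mature early | 0.84, 0.74, 0.69 | 9.9%, 13.7%, 19.1% |

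With no offset, a robust SE brought rejection back to 4.7% to 5.7%.

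**Negative binomial.** In one simulated 0/1 data set (55% vs 70%), the SE was 0.166 at zero dispersion, 0.175 at dispersion 0.2 and 0.187 at 0.5, against a robust SE of 0.110. The maximum likelihood dispersion estimate was essentially zero, which is the Poisson model again. In the first two offset settings the mean Pearson statistic per degree of freedom was below 1 (0.33 to 0.97), so a check for overdispersion would not usually be triggered.

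**Effect of a total follow-up offset on the estimate.** If maturation is equal but mean follow-up is 10% shorter in one arm, the rate ratio is 1/0.9 = 1.11 with no difference in maturation.

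**The case against.** The strongest reply is that Poisson regression with a sandwich variance is still Poisson regression. The article does not say that model-based standard errors will be used, and an analysis plan that is not shown may specify robust ones. This stands in part: the model family is not itself wrong. But the article does state a contingency, and it deals only with excess variance, when a once-only outcome has the opposite problem.

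Second, one result per index access is an inference. The secondary analysis is not limited to the index access, and the article says "New AV access surgery will be subject to data collection similar to that of the index AV access surgery". The event definitions are in an additional file that is not shown. This stands as a qualification, but counting later accesses would require its own unit and denominator.

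Third, the word rates, with an at-risk offset ending at maturation, would give an exponential survival model. Its standard error is right under a constant hazard. This also stands, so the direction of error is not fixed by the text. However, the article measures outcomes to the end-of-study event. If time does stop at maturation and some accesses never mature, the standard error can be too narrow.

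A reader might infer more than the document supports:
- That the standard errors are far too wide whatever is modelled. No maturation proportion is given, and for failure at 40% vs 25% the inflation is only 1.2-fold.
- That negative binomial would make matters worse. In practice it would not be triggered, or would collapse to Poisson.
- That maturation is the main route by which grafts are expected to win. The rationale for CVC-free days lists it with time to cannulation, thrombosis, infection and patency.

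**Conclusion.** The point holds as a correctable mismatch between outcome and model. On the natural reading (0/1 per participant, with no offset or total follow-up as offset), the model-based Poisson standard error is too wide and the stated fallback cannot correct it. Across the assumed pairs with no offset the inflation is 1.2 to 1.7-fold, and power is 20% to 57% where a correct analysis has 68% to 72%. These figures rest on assumed proportions and on 131 analysable participants per group.

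Without an offset the estimated risk ratio itself is sound. The cost is wide intervals and lost power, not false positives. With a total follow-up offset the estimate also depends on survival and retention. The outcome is secondary, and nothing here touches the primary analysis of CVC-free days.

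**What to change.** Take maturation out of the shared Poisson sentence. State that index-access maturation (or maturation failure; choose one and use it in both Table 1 and the analysis section) is a binary outcome per randomized participant. Analyse it by log-link Poisson regression with robust (sandwich) variance and no follow-up offset, or by logistic regression with a standardised risk difference. Adjust for centre and prior AV access as in the primary model. Keep count models with a person-time offset, and the negative binomial fallback, for recurrent events: adjuvant procedures, infections and other complications.

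The cost is a few sentences in the analysis section. No new data, visits or participants are needed.

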### Analysis for tertiary outcomes

Vascular Access Questionnaire scores will be obtained at 6, 12, 18 and 24 months during follow-up. We will use a linear mixed-effects model approach to compare the postoperative Vascular Access Questionnaire scores between AVF and AVG groups and to examine the longitudinal pattern in the Vascular Access Questionnaire scores over time within each treatment group. The model will include an indicator variable for treatment (AVF vs. AVG), time, and treatment by time interaction. Least square means for each group will be reported. We will test for treatment effect overall and at each time point using contrasts. Covariate adjustments will include baseline scores and the ones similar to the models used in the analysis for the primary outcome. For analyses of EQ-5D, Regret, and Tradeoffs, we will use a similar approach. For analysis of *goal concordant care regarding vascular access approach*, each participant will be classified as being concordance or not at each follow-up visit. A generalized estimating equation (GEE) model will be fit to compare the likelihood of being concordance between the AVG and AVF groups. Odds ratios (OR) averaged over time and at each time point will be reported.

### Analysis for exploratory outcomes

In these analyses we will assess the association between preoperative physical function and AV access primary failure. For these analyses, the primary predictor variable will be baseline physical function based on a composite score of grip strength, chair stand performance, clinical frailty score, and disability score. The outcome will be the incidence rate of fistula or graft primary failure. The cohort will be dichotomized at the median composite score. We will use the Cox proportional hazards model in each intervention group to explore the relationship between a baseline composite score of physical fitness and fistula or graft primary failure. Covariates included in the models will be similar to the primary analysis. The baseline composite score will additionally be modeled as a continuous variable and divided in tertiles. Receiver-operating curves will be used to compare the accuracy of the composite score that included all four markers of physical function and scores based on fewer physical function markers to a model that included the best clinical variables at predicting AV access primary failure. Areas under the curve will be compared with the method of DeLong and DeLong [35]. Similar analyses will be performed to separately test for associations between preoperative physical function and time to successful cannulation and incidence rate of adjuvant AV access procedures; and between each metric of physical function obtained at baseline and AV access primary failure.

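### The exploratory physical-function models borrow their covariates from the randomized comparison, so age and sex are not named and the association with access failure may be partly confounded (minor)

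*Protocol article*

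**What the plan says.** All of this is in the Protocol article. Under *Analysis for exploratory outcomes*, the plan states that "the primary predictor variable will be baseline physical function based on a composite score of grip strength, chair stand performance, clinical frailty score, and disability". On the cut, the plan says "The cohort will be dichotomized at the median composite score", and it adds that "The baseline composite score will additionally be modeled as a continuous variable and divided in tertiles". On the model: "We will use the Cox proportional hazards model in each intervention group". On adjustment: "Covariates included in the models will be similar to the primary analysis". The same section plans similar analyses of each physical-function measure on its own, which includes grip strength.

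The cross-reference leads to *Analysis for primary outcome*: "Covariate adjustment will include enrollment center and history of prior AV access". These are the two stratification factors listed under *Randomization*.

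Age and sex appear elsewhere in other roles. *Background* cites a meta-analysis in which "older patients have a 50–65% higher risk of primary AVF failure and 80% higher risk of secondary AVF failure compared with younger patients". *Heterogeneity of treatment effects* lists age (below 80 versus 80 and over) and sex as subgroup factors for the treatment effect. The *Discussion* presents physical function as a new predictor of access maturation that could help surgical decisions, and its closing summary speaks of factors involved in the mechanism of access failure.

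**The concern.** Center and prior AV access are a sound covariate set for AVG versus AVF, because randomization balances age, sex and everything else in expectation. Nothing balances them between patients with low and high physical function. Older patients can be expected to score lower. If grip strength differs between men and women and is scored in raw units, one cohort-wide cut will also partly sort patients by sex. If age or sex also affects access failure, part of the score's apparent effect belongs to them.

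At stake is how one exploratory result is read. The Discussion wants to say that physical function tells the surgeon something new and may bear on mechanism. Neither claim follows if the score partly restates two facts already known at the bedside. The comparison of AVG with AVF does not depend on this model.

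**Working it through.** The plan states no event count, effect size or power for this analysis, so there is no figure of its own to reproduce.

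**Step 1. Trace the covariates.** The exploratory models point to the primary analysis, and the primary analysis names center and prior AV access. Following the stated rule, neither age nor sex is a named covariate.

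**Step 2. Look for another analysis that would deal with it.**
- The continuous and tertile versions change the form of the score; no other covariates are given for them.
- Fitting each arm separately removes treatment, not age or sex.
- The ROC step compares the score with a separate model of clinical variables, which are not named. Comparing two areas under the curve does not adjust one for the other.
- The subgroup analyses test interactions of age and sex with treatment, not with the score.

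**Step 3. Size the possible bias from sex.** All inputs are assumptions, not taken from the documents: 45% women; four equally weighted standardized markers with pairwise correlation 0.4; only grip differs by sex, by 1.0, 1.5 or 2.0 within-sex SD; failure hazard ratio for women versus men (HR) of 1.0, 1.5 or 2.0; no true effect of function. A simulation of 400,000 patients gives the share of women in the low half (p_low) and in the high half (p_high) after a median split. With constant hazards, the false ratio is approximately

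ratio = [1 + p_low × (HR − 1)] / [1 + p_high × (HR − 1)]

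Composite, smallest case (gap 1.0 SD, HR 1.5): (1 + 0.513 × 0.5) / (1 + 0.390 × 0.5) = 1.2565 / 1.195 = 1.05.
Composite, largest case (gap 2.0 SD, HR 2.0): (1 + 0.551) / (1 + 0.348) = 1.15.
Grip alone, smallest case: (1 + 0.639 × 0.5) / (1 + 0.263 × 0.5) = 1.3195 / 1.1315 = 1.17.
Grip alone, largest case: (1 + 0.785) / (1 + 0.114) = 1.60.

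| Grip gap (SD) | Composite: women in low / high half | Ratio, HR 1.5 / 2.0 | Grip alone: women in low / high half | Ratio, HR 1.5 / 2.0 |
|---|---|---|---|---|
| 1.0 | 51% / 39% | 1.05 / 1.09 | 64% / 26% | 1.17 / 1.30 |
| 1.5 | 53% / 37% | 1.07 / 1.12 | 72% / 18% | 1.25 / 1.46 |
| 2.0 | 55% / 35% | 1.09 / 1.15 | 79% / 11% | 1.32 / 1.60 |

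With HR 1.0 the ratio is 1.00 throughout. Age was not simulated, because the documents give no age effect that applies within this cohort.

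**Step 4. Repeat with grip standardized within sex.** Women are then about 45% of both halves, and the composite's false ratio is about 1.00 in every scenario. This rests on the other three markers not differing by sex. If they do, and for age in any case, the terms are needed in the model.

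**Step 5. Set the bias against the precision.** With 131 patients per arm (*Sample size calculation*) and an assumed 35% risk of primary failure, each arm has 131 × 0.35 ≈ 46 events. The standard error of a median-split log hazard ratio is about 2/√46 = 0.29, so the 95% limits lie a factor of about 1.8 either side. The composite bias is log 1.05 = 0.05 to log 1.15 = 0.14, under half a standard error. For grip alone the upper end, log 1.60 = 0.47, exceeds one and a half standard errors.

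**The case against.** The strongest reply is that much of the case is read from silence or from neighbouring facts. Several stronger readings are tempting and do not hold.

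- *That grip strength is pooled raw across men and women.* The article does not say how grip is scored or how the four markers are combined. A condensed article may leave that to the full protocol or SAP.
- *That age and sex are excluded.* The cross-reference asks for similar covariates, and the primary analysis says what adjustment will include. Neither wording closes the list.
- *That the 50–65% figure sizes the age confounding here.* It contrasts older with younger patients and concerns AVFs only. Everyone in this trial is 60 or over, and half are assigned a graft.
- *That the protocol says sex affects access failure.* The heterogeneity section expects the treatment effect to vary by sex. That implies some association of sex with outcome in at least one arm, but it gives no direction, no size and nothing specific to primary failure.
- *That a positive result would merely be age and sex under another name.* The composite bias from sex is modest even under unfavourable assumptions, and the ROC step at least benchmarks the score against clinical predictors.

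These limits stand, and they reduce the claim from confounded to possibly confounded. They do not remove it. The one adjustment rule the article gives was built for a randomized contrast and is applied to a baseline marker, and no other planned analysis adjusts the score for age or sex.

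**Conclusion.** The point holds as a minor one. As written, the exploratory models name only center and prior AV access, so the association of physical function with primary failure may be partly confounded by age and sex. From sex alone, the false ratio is about 1.05 to 1.15 for the composite and about 1.17 to 1.60 for grip strength alone. This assumes a 1 to 2 SD grip gap scored without regard to sex, a failure ratio of 1.5 to 2.0 and no true effect of function. It disappears if sex does not affect failure. The contribution of age is plausible but not quantified. The larger range belongs only to one single-marker analysis, and it further assumes that grip is split at the median there. The randomized comparison and the primary, safety, cost and patient-reported outcomes are unaffected.

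**What to change.** In *Analysis for exploratory outcomes*, replace the cross-reference with a named list: center, prior AV access, age (continuous) and sex. Report the score's effect with and without age and sex, so that the reader sees how much of it they carry. State how grip is scored. If it is not already scored by sex, standardize it within sex before forming the composite and before the grip-only analysis.

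Age and sex are basic baseline data, so nothing new is collected. The cost is two degrees of freedom. Treating the seven healthcare systems as seven centers, the present model uses 6 + 1 + 1 = 8 (center, prior access, score), and the revised one 10. On the assumed 46 events per arm, that is 46/8 ≈ 5.8 falling to 46/10 = 4.6 events per degree of freedom. Diabetes and peripheral arterial disease, which *Study design* links to AVF maturation failure, would bring it to 46/12 ≈ 3.8. They are best kept optional, to be added only if event numbers allow.
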